## Abstract

**Background:**

Chronic subdural hematomas (CSDHs) are one of the most common neurosurgical conditions. The standard surgical technique includes burr-hole craniostomy, followed by intraoperative irrigation and placement of subdural closed-system drainage. The drainage is generally removed after 48 h, which can be described as fixed-time drainage strategy. According to literature, the recurrence rate is 5–33% with this strategy. In our retrospective study, postoperative hematoma volume was found to significantly increase the risk of recurrence. Based on these results, an exhaustive drainage strategy is conducted to minimize postoperative hematoma volume and achieve a low recurrence rate and good outcomes.

**Methods:**

This is a prospective, multicenter, open-label, blinded endpoint randomized controlled trial designed to include 304 participants over the age of 18–90 years presenting with a symptomatic CSDH verified on cranial computed tomography or magnetic resonance imaging. Participants will be randomly allocated to perform exhaustive drainage (treatment group) or fixed-time drainage (control group) after a one-burr hole craniostomy. The primary endpoint will be recurrence indicating a reoperation within 6 months.

**Discussion:**

This study will validate the effect and safety of exhaustive drainage after one-burr hole craniostomy in reducing recurrence rates and provide critical information to improve CSDH surgical management.

**Trial registration:**

Clinicaltrials.gov, NCT04573387. Registered on October 5, 2020.

## Administrative information

**Table Taba:** 

Title {1}	Exhaustive drainage versus fixed-time drainage for chronic subdural hematoma after one-burr hole craniostomy (ECHO): study protocol for a multicenter randomized controlled trial
Trial registration {2a and 2b}	Clinicaltrials.gov, NCT04573387. Registered on October 5, 2020. https://www.clinicaltrials.gov/ct2/show/study/NCT04573387
Protocol version {3}	2020/07/31 Protocol Version 1.0
Funding {4}	Capital Medical Development and Research Fund (grant No.2020–2-2045)

## Introduction

### Background and rationale {6a}

Chronic subdural hematomas (CSDHs) are one of the most common neurosurgical conditions. The goal of surgery is to alleviate symptoms and minimize the risk of symptomatic recurrences. The common surgical technique includes burr-hole craniostomy, followed by intraoperative irrigation and placement of subdural closed-system drainage. The drainage is generally removed after 48 h, which can be described as a fixed-time drainage strategy [1]. According to literature, the recurrence rate is 5–33% with this strategy [2–8]. Therefore, the optimal standard management procedure for CSDH remains uncertain. In our retrospective study, postoperative hematoma volume (*p* = 0.001, *B* = 0.028, Exp(*B*) = 1.028, 95% CI 1.011–1.046) was found to significantly increase the risk of recurrence [9]. Based on these results, an exhaustive drainage strategy is described to minimize postoperative hematoma volume and achieve a low recurrence rate and good outcomes.

In this treatment strategy, all patients were treated with a one-burr-hole craniostomy with irrigation and a closed drainage system. If the computed tomography (CT) scan on the first day after surgery (postoperative 24 ± 4 h) indicated that no obvious hematoma was left (hematoma showed no high density and had less than 3 mm of maximum width in axial CT scan images), the drainage catheter was removed when drainage ceased. If subdural collections remained in the hematoma cavity, the patient was treated with urokinase injection into the hematoma cavity through the catheter. The catheter was closed and reopened in 2 h, and a CT scan was performed after 24 h. If the CT scan showed no residual hematoma left, the catheter was removed when drainage ceased. However, if there was still an obvious residual hematoma, the above steps were repeated, and the patient was subjected to urokinase injection until the subdural collection was eliminated and drainage ceased.

In our experience, a total of 1126 patients with CSDH were treated with this exhaustive drainage strategy. The recurrence rate was 1.9% (21/1117), and 97.0% (1092/1117) of patients had good outcomes (modified Rankin Scale, mRS scores 0–3) at 6 months after discharge. Therefore, for evidence-based recommendations concerning CSDH management, a randomized controlled trial is needed to validate our previous results for the exhaustive drainage strategy.

### Objectives {7}

We hypothesize that compared with fixed-time drainage, exhaustive drainage after one-burr hole craniostomy reduces recurrence rates and improves clinical outcomes at 6 months in patients with CSDH. Consequently, the defined null hypothesis will be that there is no difference between the groups.

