### Trial design {8}

The ECHO trial is a prospective, randomized, open-labeled, blinded endpoint, multicenter clinical study designed to compare differences of recurrence rate and clinical outcome from operation up to 6 months postoperatively between the exhaustive drainage group and fixed-time drainage group. In total, 304 patients will be randomly assigned to the exhaustive drainage (treatment) group and fixed-time drainage (control) group at a 1:1 ratio. The Consolidated Standards of Reporting Trials (CONSORT) patient flow diagram is presented in Fig. 1.

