#### Secondary outcome

Secondary outcomes include functional outcome (modified Rankin Scale, mRS score [10] and Markwalder Grading Scale, MGS grade [11]) at baseline, and at 1, 3, and 6 months; quality of life (five-dimensional EuroQol, EQ-5D-5L [12]) at baseline, and at 1, 3, and 6 months; mortality at 6 months; and rate of complications and adverse events between groups within 6 months.

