### Statistical methods

#### Statistical methods for primary and secondary outcomes {20a}

Statistical analyses will be performed using a statistical package (SPSS software 25.0). The Kolmogorov–Smirnov test will be used to assess the normality of variables. Data for normal distribution will be presented as mean ± standard error of mean. Variables for skewed distributions will be described as median and interquartile ranges. Categorical variables will be expressed as frequencies with percentages.

Comparisons between the groups will be carried out using an independent *t*-test to compare normally distributed data, the Mann–Whitney *U* test to skewed data, and *χ*^2^ test or Fisher’s exact test to compare categorical data such as safety analyses with the incidence of AEs. For numerical data collected at different time points throughout the course of 6 months, repeated measures analysis of variance will be performed between the two groups. The significance level will be set at *p* < 0.05.

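### The clinical hypothesis is set at 6 months, but the repeated-measures ANOVA named for numerical scores has no overall term that tests the 6-month difference

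*Protocol article*

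**What the plan says.** Four places in the protocol article bear on this.

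- **Objectives {7}** states the hypothesis with a time point: "exhaustive drainage after one-burr hole craniostomy reduces recurrence rates and improves clinical outcomes at 6 months". The null is general: "the defined null hypothesis will be that there is no difference between the groups". It names no measure and no visit.
- **Trial design {8}** describes the comparison as a period. The study is to "compare differences of recurrence rate and clinical outcome from operation up to 6 months postoperatively".
- **Secondary outcome** lists the functional scores (mRS, MGS) "at baseline, and at 1, 3, and 6 months; quality of life", and gives EQ-5D-5L the same four time points. Of the outcomes measured at a visit, only "mortality at 6 months" is fixed at the end of follow-up.
- **Statistical methods {20a}** assigns one method to repeated numerical data: "repeated measures analysis of variance will be performed between the two groups". It names neither the deciding term (group or group by time) nor a 6-month contrast. The same section lists an independent t-test, the Mann-Whitney U test and chi-square or Fisher's exact test for comparisons between groups, without tying any of them to a visit.

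**The concern.** The hypothesis names one time point. The only method tied to scores measured repeatedly spans all of them. In a two-group repeated-measures ANOVA, the group term is a difference averaged over the visits in the model, and the group-by-time term asks whether the arms follow parallel courses. A significant result on either term is compatible with no difference at 6 months.

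An early gap that later closes is conceivable here. The design assumes 10% recurrence in the control arm and 2% in the experimental arm. If control patients recur, are treated again and recover before 6 months, their scores could be worse at 1 and 3 months and equal at 6. The protocol gives no timing of recurrence, so this is a scenario and not a forecast.

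The mismatch also runs the other way: a benefit present only at 6 months is diluted in the group term. At stake is whether the clinical half of the stated hypothesis gets an answer at the time point it names.

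**Working it through.** **Inputs from the protocol.** 138 evaluable patients per arm (Sample size {14}); visits at baseline, 1, 3 and 6 months (Secondary outcome); significance level 0.05 (Statistical methods {20a}), taken as two-sided because sidedness is not stated.

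**Inputs assumed.** The protocol gives no effect size, SD or correlation for mRS, MGS or EQ-5D-5L. I take SD 1 at each visit, equal correlation rho between visits from 0.3 to 0.7, and complete data.

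**The protocol's own figure.** For 10% against 2%, two-sided 5%, 80% power and pooled variance under the null:

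n = [1.96 × sqrt(2 × 0.06 × 0.94) + 0.842 × sqrt(0.10 × 0.90 + 0.02 × 0.98)]² / 0.08² = (0.658 + 0.279)² / 0.0064 ≈ 137.2, so 138 per arm and 276 in total.

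This reproduces the stated number. It concerns recurrence and is untouched by this point; it serves here only as the size per arm.

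**Formulas, for T visits in the model.**

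- Group term: z = (mean of the visit effects) / sqrt[(2/138) × (1 + (T−1)rho)/T].
- Group-by-time term: noncentral F with T−1 and 274(T−1) df, noncentrality = 69 × (sum of squared deviations of the visit effects from their mean) / (1 − rho).
- Direct 6-month test: z = effect / sqrt(2/138) = effect / 0.1204.

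**Scenario A: 0.4 SD at 1 and 3 months, zero at 6 months.** With baseline as a level, the mean effect is 0.8/4 = 0.20 and the sum of squared deviations is 4 × 0.2² = 0.16. Without baseline they are 0.8/3 = 0.267 and 0.107. For example, at rho 0.5 with baseline, the standard error is sqrt(0.01449 × 2.5/4) = 0.0952, z = 0.20/0.0952 = 2.10 and power is 56%; the noncentrality is 69 × 0.16/0.5 = 22.1 on 3 and 822 df, and power is 99%.

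| Probability of a significant result | rho 0.3 | rho 0.5 | rho 0.7 |
|---|---|---|---|
| Group term, four visits | 67% | 56% | 47% |
| Group term, three post-baseline visits | 86% | 77% | 70% |
| Interaction, four visits | 93% | 99% | 100% |
| Interaction, three post-baseline visits | 83% | 94% | 100% |
| Direct 6-month test | 5% | 5% | 5% |

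**Scenario B: 0.34 SD at 6 months only.** The mean effect is 0.34/4 = 0.085 with baseline and 0.34/3 = 0.113 without. The direct test has z = 0.34/0.1204 = 2.82.

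| Power | rho 0.3 | rho 0.5 | rho 0.7 |
|---|---|---|---|
| Group term, four visits | 18% | 15% | 13% |
| Group term, three post-baseline visits | 25% | 21% | 18% |
| Interaction, four visits | 68% | 84% | 97% |
| Interaction, three post-baseline visits | 69% | 84% | 97% |
| Direct 6-month test | about 80% | about 80% | about 80% |

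**Sensitivity to the early effect.** A simulation of the four-visit ANOVA (138 per arm, 2,000 runs per setting, same correlations) used early effects that fade to zero at 6 months.

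| Effect at 1 and 3 months | Group term | Interaction |
|---|---|---|
| 0.3 and 0.15 SD | 19-26% | 54-90% |
| 0.5 and 0.25 SD | 43-61% | 95-100% |
| 0.8 and 0.4 SD | 80-96% | 100% |

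The direct 6-month test rejected in 4-6% of runs throughout.

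**The case against.** The strongest reply is that the protocol contains no rule by which an ANOVA result becomes a 6-month claim. It says the analysis will be performed, not which term decides or how it will be read, and visit contrasts are often left to the analysis plan. This stands against a reading that is tempting: that an early difference which has vanished would be declared the hypothesised benefit. The documents do not support that; they show only that it could happen. The reply does not remove the point, because the protocol did more than stay silent: it chose a method whose overall terms do not address its own hypothesis.

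Four further replies stand in part.

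- **Baseline.** A reader might infer that baseline is pooled into the test. The methods section does not say so; it follows only from the list of time points under Secondary outcome. Dropping baseline does not remove the problem, however: the group term in Scenario A rises to 70-86%.
- **Late benefit.** It would be wrong to say that the ANOVA cannot detect a benefit confined to 6 months. The interaction has 68-97% power in Scenario B and, at rho 0.5 and above, more than the direct test. But a significant interaction shows that the profiles differ, not at which visit or in whose favour.
- **Other tests.** The listed two-sample tests could be applied at 6 months, and mRS and MGS may be handled as categorical. None is tied to that visit, so the 6-month comparison is still not named.
- **Trial design {8}.** Its wording of a comparison running from operation to 6 months suits a longitudinal analysis. Read with the Objectives, it shows two descriptions of the clinical comparison that need aligning.

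**Conclusion.** The point holds in a limited form. The Objectives set the clinical hypothesis at 6 months, and the one method assigned to numerical scores over time has no overall term that estimates or tests the 6-month difference. Under Scenario A, those terms are significant in 47-86% (group) and 83-100% (interaction) of trials with nothing present at 6 months. Under Scenario B, the group term finds a real 6-month difference in 13-25% of trials, against about 80% for the direct test.

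These sizes rest on assumed effects, correlations of 0.3 to 0.7 and complete data. A smaller early effect gives less: 19-26% for the four-visit group term at 0.3 and 0.15 SD. That neither term is the 6-month contrast does not depend on these assumptions.

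The reach is confined to secondary outcomes analysed as numerical scores. Nothing here bears on recurrence as primary outcome or on the 276 patients it requires.

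**What to change.** In Statistical methods {20a}, state that the clinical hypothesis is tested, for each score, by the between-arm difference at 6 months, reported with its estimate and 95% CI. Use baseline as a pre-treatment value, for example as a covariate, and take it off the list of outcome time points under Secondary outcome. Report the 1- and 3-month differences as supportive description of the course. A repeated-measures model can stay if the 6-month contrast from it is named as the deciding result. Align the wording of Objectives {7} and Trial design {8}, so that both say whether the clinical comparison is at 6 months or over the period.

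The cost is a few sentences of protocol or analysis-plan text and no new data, since the 6-month scores are already scheduled. The downside is that a benefit seen only early can no longer carry the 6-month claim.

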### Trial design {8}

The ECHO trial is a prospective, randomized, open-labeled, blinded endpoint, multicenter clinical study designed to compare differences of recurrence rate and clinical outcome from operation up to 6 months postoperatively between the exhaustive drainage group and fixed-time drainage group. In total, 304 patients will be randomly assigned to the exhaustive drainage (treatment) group and fixed-time drainage (control) group at a 1:1 ratio. The Consolidated Standards of Reporting Trials (CONSORT) patient flow diagram is presented in Fig. 1.

**Fig. 1 Fig1:**
[figure not shown]
Consolidated Standards of Reporting Trials (CONSORT) patient flow diagram

### Methods: participants, interventions, and outcomes

#### Study setting {9}

This is a multicenter study that will be conducted from December 2020 to May 2023 at 19 hospitals in China. In the participating centers, all patients who are diagnosed with a CSDH are tested for eligibility for the ECHO study. After gaining informed consent, patients are randomized to either the treatment or the control group. Research is facilitated by a leader center to guarantee compliance with protocol, adherence to International Conference on Harmonization-Good Clinical Practice (ICH-GCP), and data safety.

### Eligibility criteria {10}

#### Inclusion criteria

Patient (18 years to 90 years) presenting with clinical symptoms and neurological deficits of chronic subdural hematoma.Chronic subdural hematoma verified on cranial CT or magnetic resonance imaging.Written informed consent from patients or their next of kin according to the patient’s cognitive status.

#### Exclusion criteria

No clinical symptoms correlating with chronic subdural hematoma.Lack of mass effect, and no need for surgery judged clinically by neurosurgeons.Previous surgery for chronic subdural hematoma during the past 6 months.Previous intracranial surgery for any neurological disorders but chronic subdural hematoma before.Existing poor medication condition or severe comorbidity so that surgery cannot be tolerated, or follow-up cannot be completed.Severe coagulopathy or high risk of life-threatening bleeding.Postoperative cooperation is suspected to be insufficient for follow-up for 6 months.Reproductive-age women without verified negative pregnancy testing.Participating in another research.

### Who will take informed consent? {26a}

Informed consent will be obtained from all participants in the study prior to surgery of the CSDH. Based on the inclusion and exclusion criteria, patients will be screened for study participation. A verbal explanation of the written consent will be provided by the attending neurosurgeon, and any questions regarding the rationale, design, risks, and potential benefits of the study will be answered. Each participant will have sufficient time to decide whether to participate in this study. If the patient is unable to give consent, consent will be sought from a close relative. Withdrawal from the study is possible at any time, in accordance with the latest version of the declaration of Helsinki 2013.

### Additional consent provisions for collection and use of participant data and biological specimens {26b}

On the consent form, participants will be asked for permission for the research team to use their data and share them with people from relevant regulatory authorities. For this study, no biological specimens will be collected for storage.

### Interventions

#### Explanation for the choice of comparators {6b}

All participants will be treated with a one-burr-hole craniostomy with irrigation and a closed drainage system. In fixed-time drainage (control group), the drainage will be removed after 48 h postoperatively. In exhaustive drainage (treatment group), the drainage will be removed when postoperative hematoma volume is minimized with repeated urokinase injection into the hematoma cavity through a catheter based on a postoperative CT scan.

### Intervention description {11a}

#### Operation

All participants are treated with burr-hole craniostomy and a drainage system as follows. Participants undergo the surgical procedure under local anesthesia with a lateral position, and general anesthesia is performed if the participant cannot tolerate the surgery. A single 1.5-cm burr hole is drilled over the maximum width of the hematoma cavity. After coagulating with bipolar diathermy, the dura mater is opened with a cruciate incision. A soft catheter is placed carefully in all directions of the hematoma cavity for irrigating with 1000 mL warm Ringer’s lactate saline until clarification of subdural collections. The catheter is placed ½ length of the maximum diameter of the hematoma cavity toward the frontal region. After the skin is closed, the catheter is connected to a collection bag which is placed 15 cm under the head for passive drainage. During the drainage period, participants stay in bed until the drain is removed.

### Postoperative drainage strategy

In the fixed-time drainage group, the drainage will be removed after 48 h postoperatively. In the exhaustive drainage group, if the CT scan on the first day after surgery (postoperative 24 ± 4 h) indicates no obvious hematoma left(hematoma shows no high density and has less than 3 mm of maximum width in axial CT scan images), the drainage catheter will be removed when drainage ceases. If subdural collections remain in the hematoma cavity (hematoma shows high density and has more than 3 mm of maximum width in axial CT scan images), the participant will be treated with 30,000U urokinase injection into the hematoma cavity through the catheter. The catheter will be closed and reopened in 2 h, and a CT scan will be performed when drainage ceases. If the CT scan shows residual hematoma eliminated, the catheter will be removed. However, if there is still a residual subdural collection, the above steps will be repeated. If the participant is subjected to urokinase injection for 3 times, the catheter will be removed when drainage ceases.

### Postoperative follow-up CT

All participants will undergo a CT scan before the drainage is removed, before the patient is discharged from the hospital, and at 1, 3, and 6 months after surgery, retrospectively.

### Criteria for discontinuing or modifying allocated interventions {11b}

The allocated interventions cannot be modified during study participation, and crossover to the other study arm is not allowed. Cessation of the treatment is mandatory if a suspected serious adverse event (SAE) occurs, or participants request to withdraw from the study. Participants can withdraw their consent at any time and terminate their participation in the study prematurely. Withdrawal from the study and detailed reasons will be recorded if known. Moreover, the principal investigator (PI) is entitled to terminate the study prematurely if patient recruitment remains inadequate, or unacceptable risks arise after assessment by the Data Safety Monitoring Board (DSMB).

A detailed recording of all the adverse events (AEs) during the study will be closely monitored, and reported to the ethics committee as soon as possible, with the intention of a resolution or stabilization, or even termination of the study if necessary.

### Strategies to improve adherence to interventions {11c}

Study treatment takes place after enrollment, and follow-up visits take place at 1, 3, and 6 months. At enrollment, participants will receive detailed instructions about burr-hole craniostomy and the corresponding postoperative drainage strategy. Moreover, the importance of adherence to the study protocol is emphasized.

During follow-up visits at 1, 3, and 6 months, treatment adherence is monitored by asking whether the participant experiences any side effects or AEs. Study participants can contact one of the researchers with any questions during the study period. The whole study process is continuously monitored by a blinded local researcher in each center who performs the follow-up outcome measurements.

### Relevant concomitant care permitted or prohibited during the trial {11d}

Besides the study intervention, patients in both groups are treated according to the currently established standard of care at the trial center. All patients receive a standard operation and standard postoperative care. Interventions to postoperative drainage are prohibited. Any other medical treatments as parts of routine clinical practice are permitted during study participation.

